### Data collection

Data will be collected using paper questionnaires at the following time points: 1 month before surgery (T_0_), 1 week after surgery (T_1_), 2 weeks after surgery (T_2_), 3 weeks after surgery (T_3_), 6 weeks after surgery (T_4_), 2 months after surgery (T_5_) and 6 months after surgery (T_6_) (Tab. 2). If patients do not return two subsequent questionnaires, they will be contacted and kindly requested to fill in and return the next questionnaires. Video consultation will be scheduled for 1 and 3 weeks after surgery.

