### Outcomes

#### Primary outcome measure

The primary outcome is the volume of unplanned healthcare utilisation (resources used per patient). Healthcare utilisation is defined as a composite endpoint of all emergency department visits, outpatient clinic visits, rehospitalisation, patient-initiated telephone consultations with a physician or nurse, and visits to a general practitioner, allied health professionals and psychologists.

An adaptation of the Institute for Medical Technology Assessment Medical Consumption Questionnaire (iMCQ) will be used to determine the volume of healthcare utilisation and the reasons thereof. This generic questionnaire aims to determine the costs of healthcare based on care consumption and is applicable to the Dutch healthcare system [10]. The questionnaire answers will result in absolute frequencies of visits for the relevant care activities. When patients report the use of healthcare, their healthcare provider will be contacted to validate the date and the reason for the healthcare encounter. This information will be crossvalidated with the subjects’ self-reports.

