**Assessments**								
*Primary and secondary outcome measures*								
– Healthcare utilisation (iMCQ)						X		
*Tertiary outcome measures*								
– Quality of life (SF-36)	X							X
– Anxiety (HADS subscale)	X		X	X	X	X		
– Recovery (RI-10)			X	X	X	X		
*Process measures*								
– Patient satisfaction (satisfaction questionnaire)							X	
– Use of intervention (internet usage log)	X	X	X	X	X	X	X	X
*Patient and procedural data*								
– Sociodemographic data (iMCQ)	X							
– Patient characteristics (patient files)	X							
– Follow-up data (patient files)						X		

*iMCQ* Institute for Medical Technology Assessment Medical Consumption Questionnaire, *SF-36* 36-Item Short Form Health Survey, *HADS* Hospital Anxiety and Depression Scale, *RI-10* Recovery Index-10

^a^T_0_: 1 month before surgery; T_1_: 1 week after surgery; T_2_: 2 weeks after surgery; T_3_: 3 weeks after surgery; T_4_: 6 weeks after surgery; T_5_: 2 months after surgery; T_6_: 6 months after surgery

The SF-36 is routinely used at our facility and has been validated in multiple patient populations, including cardiac surgery patients [14–18]. This questionnaire assesses health-related quality of life in the previous 4 weeks. The HADS questionnaire is widely validated and is most commonly used to assess depression or anxiety. The RI-10 is a short, Dutch-language, 10-item questionnaire measuring postoperative domains on a 5-point scale over the last 7 days. It has been validated in gynaecology patients, but the general nature of the questions suits our patient population [19].

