### Limitations

The addition of our eHealth strategy to the postoperative protocol might yield additional costs in comparison to standard care. We believe that these additional costs will be balanced by reduced healthcare utilisation and will therefore result in less total costs and better patient outcomes. Another potential limitation is that we will only include patients that have sufficient computer and digital literacy skills and have access to a computer or tablet, which might diminish generalisability of our study protocol. Moreover, as in most eHealth research, our trial is not fully blinded, which could lead to bias when patients report healthcare utilisation.

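### As written, the reminder rule does not retrieve a missed T4 questionnaire, the only one carrying the primary outcome, and provider validation starts only from contacts the patient reports

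*Protocol article*

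**What the plan says.** Under Primary outcome measure, the protocol article states: "The primary outcome is the volume of unplanned healthcare utilisation (resources used per patient", summed over a composite of contact types. An adapted iMCQ "will be used to determine the volume of healthcare utilisation and the reasons thereof".

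Table 2 gives the utilisation row one mark. By column position it is at T4, level with the last HADS and RI-10 assessments. T5 carries the satisfaction questionnaire and T6 the SF-36. Data collection says that the forms are on paper and puts T4 at 6 weeks after surgery.

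The rule for non-return, in the same section, is: "If patients do not return two subsequent questionnaires, they will be contacted and kindly requested to fill in and return the next questionnaires".

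On validation, Primary outcome measure says: "When patients report the use of healthcare, their healthcare provider will be contacted to validate the date and the reason for the healthcare encounter". It adds: "This information will be crossvalidated with the subjects’ self-reports". Limitations acknowledges that "our trial is not fully blinded, which could lead to bias when patients report healthcare utilisation".

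**The concern.** A rule that waits for two consecutive missed forms and then asks for the following ones suits outcomes measured repeatedly, such as anxiety and recovery. It suits poorly an outcome measured once. If the single form is missed, later forms cannot replace it, and an analysis plan cannot recover data that nobody requested.

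The validation step has a similar weakness. It can correct or remove a contact the patient reports, but it is not triggered by a contact the patient leaves out or by a form that never arrives. Patients are not blinded, so the person deciding what is reported knows the allocation. At stake are avoidable loss of primary-outcome data and, if non-return or omission differs between arms, a biased comparison.

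**Working it through.** **1. The reminder rule, applied literally.** Inputs are the rule in Data collection and the schedule in Table 2, assuming that T0 was returned.

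| Forms missed | Contact triggered | Forms then requested | Effect on T4 |
|---|---|---|---|
| T1 and T2 | after T2 | T3 onward | prompted in advance |
| T2 and T3 | after T3 | T4 onward | prompted in advance |
| T4 alone | none | none | not retrieved |
| T3 and T4 | after T4 | T5, T6 (no utilisation items) | not retrieved |
| T4 and T5 | after T5 | T6 (no utilisation items) | not retrieved |

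There are 2 × 2 × 2 = 8 return patterns over T1 to T3. Three trigger contact before T4: all three forms missed, only T1 and T2 missed, only T2 and T3 missed. Five do not. In none of the eight does the rule request a T4 form already missed. These are counts of patterns, not proportions of patients.

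**2. The validation rule.**
- Contact reported: the provider is approached and date and reason are checked.
- Contact omitted, provider named for another contact: it might surface in the cross-check.
- Contact omitted, provider not named: no check is triggered.
- T4 form not returned: no check is triggered.

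Table 2 also marks follow-up data from patient files at T4. The items listed under Patient and procedural data are clinical events (deaths, repeat operations, deep sternal infections, strokes, new infarctions). They do not rebuild the utilisation composite.

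**3. The plan's sample size, reproduced.** Inputs from Sample size calculation: d = 0.35, α = 0.05 (taken as two-sided), power 0.80, 1:1 allocation.

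n per arm = 2 × (1.96 + 0.8416)² / 0.35² = 2 × 7.849 / 0.1225 = 128.1, so 129 per arm and 258 in total. The t-test version gives 129.1, so 130 per arm and 260 in total, as stated. The allowance is (280 − 260) / 280 = 7.1%, which the article means to cover loss to follow-up and nonadherence together.

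**4. Power if T4 forms are missing.** The loss rates m are assumptions. With n = 140 × (1 − m) per arm, the normal approximation is power ≈ Φ(0.35 × √(n/2) − 1.96). For m = 10%, n = 126, and 0.35 × √63 − 1.96 = 0.818, giving 0.793.

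| Assumed T4 loss | n per arm | Power, normal | Power, t-test |
|---|---|---|---|
| 0% | 140 | 0.834 | 0.831 |
| 7.1% | 130 | 0.806 | 0.803 |
| 10% | 126 | 0.793 | 0.790 |
| 15% | 119 | 0.770 | 0.767 |
| 20% | 112 | 0.745 | 0.741 |

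**5. How sensitive the design is to unequal reporting.** The article cites 0.88 ± 0.15 without saying whether 0.15 is a standard deviation. If it is, the design effect is 0.35 × 0.15 = 0.0525 contacts, and 0.0525 / 0.88 = 6.0% of the mean. With an assumed SD of 0.5 or 1.0 it is 0.175 / 0.88 = 20% or 0.35 / 0.88 = 40%. A net reporting difference between arms of that size would equal the whole planned effect. This sets a scale; it does not estimate any bias.

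**The case against.** A reader might infer that the rule never pursues T4 at all. It does: patients who miss T1 and T2, or T2 and T3, are an obvious risk group for a missing T4, and they are asked for it beforehand. Only a T4 form already missed is not retrieved.

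A reader might also infer that such data are certainly lost. The article is condensed and does not exclude other retrieval, and the full protocol may hold more operational detail. Standard care includes an outpatient visit 6 weeks after discharge, close to T4, although nothing says that forms are collected there. Patient files would show some major events. This limits the claim to the rules as stated, but those rules fix a trigger and an action that do not serve the primary outcome.

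Bias between arms is likewise not shown. The article does not say that unwell patients return fewer forms or that video consultations affect returns or reporting. The nurse practitioner conducting them is to be kept unaware of the specific outcomes. The article itself discloses reporting bias as a limitation, but the validation step described does not address omitted contacts.

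The power figures have limits. The loss rates are assumed and include deaths and withdrawals that no reminder recovers. They use the t-test that reproduces the plan's N, whereas the planned test is Mann-Whitney. The abstract makes 280 a minimum. The figures illustrate consequence and reveal no error in the sample size.

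**Conclusion.** The point holds in limited form. The primary outcome is collected once, the stated rule does not request a T4 form after it is missed, and validation cannot detect omitted contacts with providers the patient does not name. This rests on a literal reading of the rule and on the T4 position of the single mark in Table 2.

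The loss of power is modest: it falls below 0.80 once more than about 7% of 280 T4 forms are missing, and to about 0.74 at an assumed 20%. Differential loss or under-reporting is the more serious possibility, but the document neither shows nor quantifies it. The change is worth making because these data can be recovered cheaply.

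**What to change.** - Send a reminder for any single unreturned T4 form, request T4 itself, and complete the iMCQ by telephone if it still does not arrive. Record the mode of completion.
- For every randomised patient in both arms, whether or not contacts are reported, extract emergency visits, outpatient visits and readmissions at the trial hospital from the patient files already reviewed at T4.
- State that this extraction does not cover GP, allied-health, psychologist or other-hospital contacts, which remain self-reported. Telephone completion helps with these in non-returners but does not reveal omissions.

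The cost is a few more patient contacts, mixed modes for some T4 data, and some extra record extraction. The endpoint and the sample size do not change.

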### Statistical considerations

#### Data analysis

Descriptive statistics will be used to summarise baseline characteristics of the study population. Healthcare utilisation will be expressed as mean ± standard deviation (resource use per patient) and absolute and relative frequencies (users per resource). Mann-Whitney U test and Fisher exact test will be used to compare the intervention and control group. Multivariate regression analysis will be performed to adjust the outcomes for confounding factors based on univariate analysis (*p* < 0.1), literature review and expert opinion.

The primary analysis will be an intention-to-treat analysis. In the secondary analysis, we will compare the control group with the intervention group that used the educational videos at least once and completed the video consultations (‘users only’). A *p*-value <0.05 will be considered statistically significant and all analyses will be performed using SPSS 25 (SPSS Inc., Chicago, IL, USA).

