**Methods:**

For this single-centre randomised controlled trial, at least 280 patients referred for CABG will be included at the preoperative outpatient clinic and randomised to an intervention or control group. The intervention group will have access to an eHealth programme, which consists of online educational videos developed by the Dutch Heart Foundation and postoperative video consultations with a physician. The control group will receive standard care and will not have access to the eHealth programme. The primary endpoint is healthcare utilisation; other endpoints include anxiety, duration of recovery, quality of life and patient satisfaction. Participants will complete several questionnaires at 6 time points during the study.

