#### Tertiary outcome measures

Tertiary outcome measures are the patients’ quality of life and their mental and physical status. To assess these domains, the 36-Item Short Form Health Survey (SF-36) [11], the anxiety subscale of the Hospital Anxiety and Depression Scale (HADS) [12] and an adaptation of the Recovery Index-10 (RI-10) [13] will be used at different time points during follow-up (Tab. 2).

**Table 2 Tab2:** Schedule of enrolment, interventions and assessments

	Time point^a^							
	Enrolment	Surgery	Follow-up					
Variable	*T*_*0*_		*T*_*1*_	*T*_*2*_	*T*_*3*_	*T*_*4*_	*T*_*5*_	*T*_*6*_

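### The adjustment rule does not commit to the T0 HADS anxiety and SF-36 scores, and no longitudinal model is named for HADS or RI-10, which risks avoidable loss of precision on tertiary outcomes

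*Protocol article*

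**What the plan says.** The protocol article's Data analysis section first describes how healthcare utilisation will be summarised. It then says "Mann-Whitney U test and Fisher exact test will be used to compare the intervention and control group", without naming an outcome. The next sentence is the adjustment rule: "Multivariate regression analysis will be performed to adjust the outcomes for confounding factors based on univariate analysis" at p < 0.1, together with "literature review and expert opinion". This sentence refers to the outcomes in the plural and is the only adjustment rule given. Patient and procedural data adds that patient data may be used to adjust endpoints where needed.

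On the outcomes concerned: "Tertiary outcome measures are the patients’ quality of life and their mental and physical status". Table 2 schedules them as follows:

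- HADS anxiety: T0, T1, T2, T3, T4
- RI-10 recovery: T1, T2, T3, T4, with no T0 score
- SF-36 quality of life: T0 and T6

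The abstract says that "other endpoints include anxiety, duration of recovery, quality of life and patient satisfaction".

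**The concern.** In a 1:1 randomised trial, covariate adjustment serves precision and removes chance imbalance. The covariate that usually does most is the baseline value of the same scale, and here it is already collected for two of the three instruments. The stated rule treats it as a possible confounder to be discovered, not as a covariate fixed in advance.

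The rule also does not say what the univariate screen is run against. If it is the outcome, the T0 score will usually pass, but the model still depends on the data. If it is treatment arm, randomisation means that a T0 score passes only about 10% of the time at p < 0.1, so a strong predictor would be left out about 90% of the time unless literature or expert opinion brought it in.

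The abstract's hypotheses include less anxiety and faster recovery. HADS and RI-10 are each measured at four follow-up times, yet the article names no method that uses those times together. What is at stake is precision on the tertiary hypotheses.

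**Working it through.** **Inputs from the article.** Sample size calculation: d = 0.35 (set for the primary outcome), α = 0.05, power 0.80, 260 required and 280 planned. Table 2: the visit schedule above.

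**Assumptions, not in the article.** Correlation r between T0 and follow-up, taken as 0.4 to 0.6; an effect of 0.3 SD on a tertiary scale; 130 analysed per arm; two-sided α = 0.05. The four-visit figures also assume compound symmetry (the same r between every pair of measurements, T0 included) and an effect that is constant over T1 to T4.

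**Step 1: the article's own figure.** Normal approximation: n per arm = 2(1.960 + 0.842)² / 0.35² = 128.1, so 129 per arm and 258 in total. The two-sample t-test gives 129.1, so 130 per arm and 260 in total. The stated 260 reproduces as a two-sided calculation; one-sided would give 202.

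**Step 2: one follow-up score, with and without T0.** Power = Φ(d·√(n / 2v) − 1.96), where v is the residual variance relative to the raw variance. With d = 0.3 and n = 130, d·√(n/2) = 0.3 × √65 = 2.419.

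| Analysis | v | Standardised effect | Power |
|---|---|---|---|
| Unadjusted t-test | 1 | 2.419 | 0.68 |
| Mann-Whitney (efficiency 0.955 for normal data) | 1/0.955 | 2.364 | 0.66 |
| ANCOVA, r = 0.4 | 1 − 0.16 = 0.84 | 2.639 | 0.75 |
| ANCOVA, r = 0.5 | 1 − 0.25 = 0.75 | 2.793 | 0.80 |
| ANCOVA, r = 0.6 | 1 − 0.36 = 0.64 | 3.023 | 0.86 |

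Adjustment removes 16%, 25% and 36% of the variance. Nearly all of the gain comes from the T0 score; the choice of unadjusted test accounts for only 0.66 against 0.68. At the article's d = 0.35, the same formula gives 0.81 unadjusted and 0.87, 0.90 and 0.94 with ANCOVA.

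**Step 3: four follow-up visits.** The variance of the mean of four visits, relative to one visit, is (1 + 3r)/4. With T0 adjustment it is (1 + 3r)/4 − r².

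| r | RI-10 (no T0 score) | HADS (with T0 score) |
|---|---|---|
| 0.4 | 0.55 | 0.55 − 0.16 = 0.39 |
| 0.5 | 0.625 | 0.625 − 0.25 = 0.375 |
| 0.6 | 0.70 | 0.70 − 0.36 = 0.34 |

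So RI-10 keeps 55% to 70% of the single-visit variance, and HADS keeps 34% to 39%. SF-36 has one follow-up, so only Step 2 applies to it.

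**Step 4: would the screen find the T0 score?** If the screen is against the outcome, with 260 patients and p < 0.1, the chance of selection is about 0.49 at r = 0.1, 0.95 at r = 0.2 and above 0.999 at r = 0.3 or more. A useful baseline score would then nearly always enter. That is a reason to name it beforehand, since the screen adds nothing except dependence on the data.

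**The case against.** The best case for the plan has four parts.

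- **The tests may concern utilisation only.** A reader might infer that anxiety, recovery and quality of life are to be compared by Mann-Whitney. The article does not say so. The sentence follows directly on the utilisation summaries, and its two tests match them: Mann-Whitney for resource use per patient, Fisher for users per resource. This stands. The point therefore rests on the adjustment rule, which does speak of the outcomes generally.
- **The T0 score is not excluded.** Literature review and expert opinion are both open routes, and Step 4 shows that a screen against the outcome would usually select it. This also stands: T0 is uncommitted, not discarded.
- **A fuller plan may give the tertiary models.** It may, and the absence of a longitudinal model from a condensed article would not be a finding by itself. But the article does state a covariate rule, and a plan that followed it would inherit its weakness.
- **The size depends on assumptions.** No correlation is given in the article. Compound symmetry lets a score taken a month before surgery correlate with recovery scores as strongly as those correlate with one another, which is generous. A constant effect also sits uneasily with an interest in speed of recovery. The four-visit figures are illustrative.

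A reader might also infer four separate visit-wise tests and an inflated false-positive rate. No such tests are set out anywhere in the article, so that charge is not made.

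**Conclusion.** The concern holds as a matter of precision on tertiary outcomes. The stated rule leaves the T0 HADS anxiety and SF-36 scores to a selection step, when always including them uses the same data and is better. For correlations of 0.4 to 0.6, that step puts 16% to 36% of the variance at stake for a single follow-up score, which is power of about 0.66 against 0.75 to 0.86 at 0.3 SD and 130 per arm. This is the loss if T0 is left out; if it is selected, most of the loss disappears.

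The instruments differ. Only HADS has both a T0 score and repeated follow-up, so the 34% to 39% figure belongs to HADS alone. RI-10 can gain only from its repeated visits, and SF-36 only from its baseline.

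The documents do not support a stronger reading. The primary outcome (iMCQ at T4), the 260/280 sample size and the validity of the randomised comparison are unaffected. Table 2 places both allocation and the T0 questionnaires at enrolment, but the order in which they happen is a matter of trial conduct and is not part of this point.

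**What to change.** In Data analysis, add a short statement for the tertiary outcomes:

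- **SF-36 at T6:** ANCOVA with arm and the T0 score.
- **HADS anxiety:** mixed model for repeated measures over T1 to T4 with arm, visit, arm-by-visit and the T0 score.
- **RI-10:** the same mixed model without a baseline term, with the arm and arm-by-visit contrasts as the recovery comparison.
- **Covariates:** for HADS and SF-36 the T0 score is always included, and the p < 0.1 screen is dropped.

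This changes analysis wording only. It needs no new data, no extra patients and no change to the visit schedule, and the models are available in the software that the article names.

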**Objectives:**

We aim to evaluate whether the use of an eHealth programme can reduce unplanned healthcare utilisation and improve mental and physical health in the first 6 weeks after discharge in patients who underwent CABG. In addition, patient satisfaction and use of the eHealth programme will be evaluated.

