## Introduction

Coronary artery bypass graft grafting (CABG) is the most prevalent cardiac surgery performed in the Netherlands, with roughly 7000 procedures annually [1]. The care chain of CABG is costly, and several quality improvement initiatives have been successfully implemented that sought to contain costs and to improve patient outcomes [2, 3]. Despite the positive effects of these initiatives on costs, mortality, postoperative morbidity and process measures such as in-hospital length of stay, healthcare utilisation in the first 30 days after CABG remains an issue, placing a significant burden on the healthcare system. Readmissions after CABG are commonly reported and the readmission rate can be as high as 34% in the first 30 days [4, 5].

Insight into unplanned healthcare utilisation during this period is scarce (apart from readmissions), but it is reasonable to expect a short hospital stay after CABG is counterbalanced by the use of other healthcare services, especially because planned care is not initiated until 6 weeks after discharge. In this period, patients commonly experience psychological symptoms (e.g. anxiety, depression), have to deal with uncertainty and worry about what to expect (e.g. what level of postoperative pain is normal, is physical exercise allowed?) [6]. Recall of information provided perioperatively is often incomplete and patients do not always know who to contact in case of complaints. They will then search for (sometimes unreliable) information on surgery or recovery and reach out to different healthcare providers, who have a varying degree of expertise in CABG care. Conflicting advice on recovery can further increase fear and insecurity, which will eventually hamper the recovery process and contribute to unplanned healthcare utilisation [7, 8].

We hypothesise that restructuring the postoperative period with an eHealth strategy will reduce unplanned healthcare utilisation through improved mental and physical health and faster recovery. In the IMPROV-ED trial, we aim to evaluate whether the use of an eHealth programme that consists of educational videos developed by the Dutch Heart Foundation (*Hartstichting*) and video consultations, is more effective than standard care in the reduction of unplanned healthcare utilisation and the improvement of patient outcomes in the first 6 weeks after CABG. In addition, a process and patient satisfaction evaluation of the newly developed eHealth strategy will be conducted.

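### The secondary users-only analysis selects intervention patients by what they do after randomisation and during the outcome period, so it can show a difference when the programme has no effect

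*Protocol article*

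**What the plan says.** The Data analysis section sets the hierarchy: "The primary analysis will be an intention-to-treat analysis". In the secondary analysis, labelled users only, "we will compare the control group with the intervention group that used the educational videos at least once and completed the video consultations". The same section says of testing that "Mann-Whitney U test and Fisher exact test will be used to compare the intervention and control group", with a 0.05 significance threshold. No restriction is placed on the controls.

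Three other statements bear on this:

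- **Timing of consultations.** The Data collection section states: "Video consultation will be scheduled for 1 and 3 weeks after surgery". As extracted, Table 2 marks them at T2 and T4, which its footnote defines as 2 and 6 weeks after surgery.
- **Outcome and its period.** The aim is to "reduce unplanned healthcare utilisation and improve mental and physical health in the first 6 weeks after discharge". The Primary outcome measure section begins: "Healthcare utilisation is defined as a composite endpoint of all emergency department visits, outpatient clinic visits, rehospitalisation". It then adds patient-initiated telephone consultations and visits to general practitioners, allied health professionals and psychologists. The questionnaire that measures these (iMCQ) is collected at T4, 6 weeks after surgery.
- **Access.** The abstract says: "The control group will receive standard care and will not have access to the eHealth programme".

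The plan also foresees regression adjustment for confounders. The Patient and procedural data section lists comorbidities, in-hospital complications and length of stay among the data that may serve for it.

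**The concern.** Being a user is not a baseline characteristic. It is settled after randomisation and after surgery, while the outcome is accruing. To qualify, a patient must be available and able at each consultation. A readmission or serious illness can prevent that, and a readmission is itself a component of the endpoint. A patient who misses a consultation for such a reason leaves the intervention side. A control with the same course who returns the 6-week questionnaire remains. The two groups then differ in prognosis whether or not the programme works.

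The article cites literature in which "the readmission rate can be as high as 34% in the first 30 days", so events of this kind need not be rare. Users only is the one comparison set named besides intention-to-treat, and it falls under the same significance threshold. A reader could take a significant result from it as evidence of efficacy among those who take up the programme, which the design of the comparison cannot support.

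**Working it through.** **The plan's own figure.** The plan gives no figure for the users-only analysis. Its sample size reproduces: d = 0.35, two-sided α = 0.05 and power 0.80 give 129.1 per arm by the t-test, so 130 per arm and 260 in total. The point does not depend on this; d = 0.35 serves only as a yardstick.

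**Model 1: early contacts cause missed consultations.**

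From the document: mean 0.88 contacts per patient (Sample size calculation) and 140 per arm. Assumed: no programme effect; gamma frailty f with shape 1 and mean 1; early and late contacts each Poisson(0.44 f), so half are early; each early contact carries a chance q of a missed consultation. A patient with E early contacts is then a user with probability (1 − q)^E.

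- Share of users = 1 / (1 + 0.44q)
- Mean in users = 0.44(2 − q) / (1 + 0.44q)
- SD in controls = √(0.88 + 0.88²) = √1.6544 = 1.286. This is the model's SD, not the 0.15 quoted in the article.

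| q | Share of users | Mean in users | Below 0.880 by | Spurious d |
|---|---|---|---|---|
| 0.1 | 1/1.044 = 96% | 0.836/1.044 = 0.801 | 9% | 0.079/1.286 = 0.06 |
| 0.2 | 1/1.088 = 92% | 0.792/1.088 = 0.728 | 17% | 0.152/1.286 = 0.12 |
| 0.3 | 1/1.132 = 88% | 0.748/1.132 = 0.661 | 25% | 0.219/1.286 = 0.17 |

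At q = 0.3 the artefact is about half the design effect (0.17/0.35 = 0.49). Simulating this model with 140 per arm and the Mann-Whitney test gives a false significant benefit in about 6–7%, 14% and 27–29% of trials (two separate runs), where 2.5% is nominal.

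**Model 2: completion depends on underlying morbidity.**

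Assumed: gamma-Poisson counts with dispersion 1, no programme effect, 140 per arm, and an odds ratio (OR) for completion per SD of morbidity. 2,000 runs per scenario.

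| Mean | OR | False benefit at 90 / 70 / 50% completion |
|---|---|---|
| 0.88 | 1 | 2.1 / 2.0 / 2.5% |
| 0.88 | 0.7 | 4.3 / 6.5 / 10.2% |
| 0.88 | 0.5 | 5.8 / 14.1 / 22.3% |
| 3 (assumed) | 0.5 | 8.0 / 22.7 / 33.4% |
| 0.88 | 1.5 | 1.3 / 0.5 / 0.2% |

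At OR 1 there is no bias. At OR 1.5, where sicker patients complete more often, the users' mean rises to 0.906 / 0.966 / 1.044 and the bias runs against the programme. The intention-to-treat test rejected in 3.6–5.6% of runs across all scenarios, close to its nominal 5%.

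**Case mix.** Suppose 34% have a complicated course (the upper readmission figure cited, used as a proxy) and complete at 50%, against 85% of the others (both assumed). The complicated share among users is 0.34 × 0.50 / (0.34 × 0.50 + 0.66 × 0.85) = 0.170/0.731 = 23%, against 34% of controls. With 20% complicated it is 0.100/0.780 = 12.8% against 20%.

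**The case against.** The strongest reply is that the protocol already ranks this analysis correctly. Intention-to-treat is primary, users only is secondary, and an adherent-set analysis beside intention-to-treat is common. That stands, and it limits the weight of the point. The article does not say that the trial's conclusion may rest on the users-only result, and how it will be presented is not known.

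Four further objections:

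- **Direction.** A reader might infer that the comparison must favour the programme. The documents do not support that: they give no completion rates and no reasons for non-completion. The consultations deal with recovery and complaints, so patients with more complaints might attend more often, and the bias would then reverse.
- **Certainty.** A reader might infer that the analysis will show a benefit from selection alone. Even at q = 0.3, most simulated trials showed no significant benefit.
- **Deaths.** A reader might infer that deaths are removed from the intervention arm only. The outcome comes from a questionnaire at 6 weeks, so death before then can remove outcome data in both arms. The asymmetry concerns patients who miss a consultation but still return that questionnaire, and controls like them.
- **Mechanism.** Model 1 treats all early contacts alike. A telephone call or a general practitioner visit hardly prevents someone from joining a remote consultation, so the upper values of q may be generous.

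The planned regression deserves mention but is no remedy. It reaches measured factors only, and adjusting for events after randomisation does not make the groups comparable again.

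**Conclusion.** The point holds as a weakness of a secondary analysis that should be corrected. The users-only contrast is unbiased under no effect only if completion is unrelated to prognosis, and nothing in the article supports that condition. The likely direction is in favour of the programme, but this is not certain.

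The illustrative size is a users' mean 9–25% below control (d = 0.06–0.17) with no true effect. Where sicker patients complete less often, a false significant benefit occurs in roughly 4–33% of trials against 2.5% nominal. These ranges rest on assumed missing chances, completion rates, dispersion, early/late split and, in part, an assumed mean of 3. They show what is possible and do not predict this trial. The intention-to-treat result is unaffected.

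**What to change.** **Preferred.** Replace the users-only comparison with a complier-average causal effect that uses randomisation as the instrument and keeps all randomised patients. Controls have no access by design, so nonadherence is one-sided and the estimate is the intention-to-treat difference in means divided by the share of users. With no effect the numerator has expectation zero, whoever completes. Define a user as anyone with any use of the programme (a video or a consultation). Under the present definition, patients who watched videos but missed a consultation count as untreated although the programme may have affected them, and the exclusion restriction becomes implausible.

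**Alternative.** Keep the comparison as descriptive only, without a p-value or causal wording.

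**Cost.** A change of wording and a short analysis; Table 3 already provides for recording portal logins and completed consultations. The interval widens: relative to intention-to-treat, by about 1/share, so 1.11, 1.43 and 2.00 times at 90, 70 and 50% users. The present comparison gives √((1 + 1/share)/2) = 1.03, 1.10 and 1.22 times (equal SDs assumed). The any-use definition also changes the question: it does not target full completion, and if nearly everyone logs in once the estimate lies close to intention-to-treat.

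**Also reconcile** the consultation times in the Data collection section with those in Table 2, since they determine when a patient can qualify as a user.
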